#### Analysis of MRI data

For structural MRI analysis, image processing will be performed using FSL 4.1 (FMRIB Software Library; www.fmrib.ox.ac.uk/fsl/) and an in-house software developed in Matlab (version 6.5, The MathWorks), with procedures similar to those described earlier (67–70). Using T1 anatomical image, we will identify and segment hippocampi and amygdala. Concerning diffusion weighted imaging, a diffusion tensor imaging model will be fit at each voxel, generating mean diffusivity (MD) maps. The MD maps were then registered to brain-extracted whole-brain volumes from T1-weighted images using a full affine (correlation ratio cost function) alignment with nearest-neighbor resampling. As a result of this processing, the MD maps were corrected for head movements, and shared an identical reference space with the anatomical T1-weighted volumes. For standard volumetric analysis, we will extract volume values from each segmented structure and divided this value by the total intra-cranial volume (TIV) to normalize for participant′s brain size. For each subject, the region of interest segmentation results, coregistered MD were all superimposed onto the original T1-weighted volume. The segmented structures defined the binary masks, where the mean values of MD will be calculated for each individual.

For functional MRI analysis, image processing will be performed using SPM12 (https://www.nitrc.org/projects/spm), CONN toolbox (https://www.nitrc.org/projects/conn) and an in-house software developed in Matlab (version 6.5, The MathWorks). Individual correlation maps between the defined regions (hippocampus, amygdala, anterior cingulate gyrus, frontal cortex—these areas of interest are anatomical zones defined in known and classical stereotactic spaces in neuroimaging) and the whole brain will be determined. The coordinates of the regions are identical for each subject because the images are in an identical (MNI) space. The correlation indices will be transformed into normally distributed variables using the Fisher transformation. These maps will then be used to carry out a *t*-test, corrected for multiple comparisons, between the maps of different groups. This will allow us to determine the intensity and extent of synchronous activity in the cerebral zones functionally connected to the hippocampus, the amygdala, and the prefrontal cortex.

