### Outcomes

The primary outcome will be the TSPO density assessed by the volume of cerebral distribution of the tracer [18F]DPA-714 in the currently depressed group vs. the control group.

The secondary outcomes will be: (1) the TSPO density evaluated by the brain distribution volume of the [18F]DPA-714 tracer in the currently depressed vs. remitted depressed groups, (2) the clinical severity assessed by the Montgomery and Asberg Depression Scale—MADRS), BAS (Brief Scale for Anxiety), and the Columbia-Suicide severity rating scale—CSSRS), (3) MRI imaging: (i) structural (i.e., cortical thickness to quantify cortical atrophy); (ii) diffusion (i.e., the mean diffusivity for measuring microstructural integrity); (iii) T2^*^ relaxometry (i.e., the R2^*^ for measuring intracerebral iron content), and (iv) resting-state functional MRI (i.e., default mode network connectivity strength), (4) the concentrations of biological markers of peripheral inflammation (i.e., hs-CRP, IL-6, TNF alpha).

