#### Analysis of all data

PET and MRI imaging, clinical symptomatology and biological markers. PET and MRI images will be co-recorded using a method previously used by our team (71) [e.g., 71] so that the maps of all multimodal markers have the spatial consistency needed for their statistical comparison. Firstly, for each marker map, we will perform *t*-tests to compare the groups with each other (SPSS 25.0). This will allow us to quantify the structural, functional and inflammatory alterations that characterize each group (i.e., treatment-resistant MDD vs. control, responsive MDD vs. control, treatment-resistant MDD vs. responsive MDD). Secondly, we will verify that there is no spatial collocation between the atrophy marker (MRI) and the inflammation marker (DPA714 -PET) that can induce a different interpretation of PET results. Finally, we will correlate the inflammation marker maps with the structural and functional marker maps generated with MRI. This will allow us to understand whether neuroinflammation is linked to brain changes (e.g., iron deposits, functional alteration).

To study the correlation between the severity of depressive symptoms, suicide risk and the intensity of neuroinflammation, graphic representations will be made to observe the distribution of these data in the two groups concerned. The Pearson correlation coefficient will be calculated in each instance. The same analysis strategy will be used to measure the correlation between plasma concentrations of biological markers of peripheral inflammation and the intensity of neuroinflammation in the three study groups.

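### Mean diffusivity is a plain average over a binary T1 mask with no stated guard against CSF at the edge, so a raised value need not mean loss of microstructural integrity

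*Protocol article*

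**What the plan says.** Under Analysis of MRI data, the protocol article defines the regions first: "Using T1 anatomical image, we will identify and segment hippocampi and amygdala". The MD map is then registered to the T1 volume "using a full affine (correlation ratio cost function) alignment with nearest-neighbor resampling". The summary per subject follows: "The segmented structures defined the binary masks, where the mean values of MD will be calculated for each individual".

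The same section also provides for volumetry: "we will extract volume values from each segmented structure and divided this value by the total intra-cranial volume (TIV"). That normalised volume is not linked to MD anywhere.

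Outcomes states how MD will be read: "the mean diffusivity for measuring microstructural integrity". Analysis of all data plans unadjusted t-tests between groups for each marker, and then "we will correlate the inflammation marker maps with the structural and functional marker maps generated with MRI". Its one safeguard against atrophy is that "we will verify that there is no spatial collocation between the atrophy marker (MRI) and the inflammation marker (DPA714 -PET"), and the reason given there is the interpretation of the PET results.

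**The concern.** A voxel at the border of the hippocampus or amygdala can hold both tissue and CSF. In a plain mean over a binary mask it has the same weight as a voxel deep inside the structure. The error always runs upward, because CSF has the higher diffusivity. If the share of CSF inside the mask differs between groups, MD differs between groups even when the tissue is the same.

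The plan would then label the difference as microstructural. It recognises that atrophy can mislead the reading of PET, but it has no matching step for MD, although it already extracts the volume that such a step would use. At stake are the MD group comparisons and the MD part of the secondary objective that correlates PET with structural MRI markers.

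**Working it through.** The plan gives no figure for MD, so there is none to reproduce. It states no diffusion voxel size, MD spread or expected atrophy. Every number below rests on assumptions and shows direction and rough scale only.

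**1. Mixing model.** With a CSF share f in the mask,

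MD_mean = (1 - f) × MD_tissue + f × MD_CSF.

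The relative rise per percentage point of CSF is (MD_CSF - MD_tissue) / MD_tissue, in percent. Assume tissue 0.75 to 1.0 and CSF 2.8 to 3.2 (×10⁻³ mm²/s):

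- lowest: (2.8 - 1.0) / 1.0 = 1.8% per point
- highest: (3.2 - 0.75) / 0.75 = 3.3% per point

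A small CSF share therefore matters. What the model does not say is how far that share would differ between groups.

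**2. Phantom.** An ellipsoid was averaged to diffusion voxels, resampled by nearest neighbor, and its mean taken over the binary mask. Assumed inputs: tissue MD 0.8 and CSF 3.0; volumes 3500 and 1500 mm³; voxels 2.0 or 2.5 mm; CSF on 20% or 40% of the surface; misalignment 0 or 1 mm towards CSF; shrinkage 0, 10 or 20%. True tissue MD was 0.800 throughout.

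| Change, tissue intact | Effect on full-mask mean MD |
|---|---|
| Level, all scenarios | 0.836 to 1.093, i.e. 4.6% to 37% above 0.800 |
| Shrinkage of 10 to 20% alone | -0.1% to +2.2% |
| 1 mm misalignment towards CSF | +4% to +14% |
| 10% shrinkage with CSF contact rising from 20% to 40% | +7.8% to +12.7% |
| Mask eroded by about one diffusion voxel, level | 0.800 to 0.819, i.e. 0% to 2.3% above 0.800 |

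**3. Which part drives it.** Take the 3500 mm³ structure, 2.0 mm voxels, no misalignment. The mean is 0.8364 at 20% contact and 0.8961 at 40% contact without shrinkage: 0.8961 / 0.8364 = 1.071, or +7.1%. Adding 10% shrinkage gives 0.9016 / 0.8364 = 1.078, or +7.8%. Nearly all of the rise comes from CSF contact and little from the smaller volume.

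**4. Shrinkage alone against the spread.** Assume a between-subject SD of MD of 5 to 8%. The largest shrinkage-only shift is then 2.2 / 8 = 0.28 SD to 2.2 / 5 = 0.44 SD. A two-sided two-sample t-test at 20 versus 20 would reject in about 14% to 27% of trials. This is purely illustrative.

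**5. What the phantom does not test.** It checked erosion only. It did not check exclusion of CSF-level voxels or the median, and it did not model differences between subjects.

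**The case against.** The strongest reply is that this is a condensed article. It says processing follows procedures similar to earlier published ones, and those sources or the full protocol may contain erosion or CSF exclusion. That possibility stands. But the article does not leave the method open: it names the registration type, cost function, resampling, mask type and summary statistic. Followed as written, edge voxels count in full. If a guard exists, one sentence would state it.

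Three stronger readings are tempting, and the documents support none of them.

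- **Atrophy will appear as microstructural loss.** Shrinkage alone had little effect in the phantom. The Introduction reports prefrontal thickness and striatal volume, and the hypothesis speaks of frontal-subcortical circuits in general; neither predicts volume loss in the hippocampus or amygdala. Misalignment that is equal across groups shifts every group alike and creates no difference.
- **A large false effect is likely.** A 2-point group difference in CSF share, at 2 to 3% per point and an SD of 5 to 8%, gives 4/8 = 0.5 to 6/5 = 1.2 SD, and 34% to 96% rejection. But the 2 points are chosen, not derived. If CSF share also varies between subjects with an SD of 3 points, on top of a 4 to 6% spread in MD, the total SD is √(6² + 4²) = 7.2% to √(9² + 6²) = 10.8%. The same difference is then 0.47 to 0.61 SD, with 31% to 47% rejection. None of these is an estimate for this trial.
- **A negative PET-MD correlation is built in.** PET regions come from the MNI-AAL atlas and MD from T1-segmented masks, so the CSF share is not shown to be common to both. The amygdala is not in the PET region list. Pooling to 60 subjects is not stated; with 20, an assumed r of -0.20 to -0.26 would be significant in only about 13% to 20% of trials.

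**Conclusion.** The concern holds in a limited form. As described, the MD summary is open to upward bias from CSF at the mask edge. A group difference in CSF contact, atrophy or alignment can therefore be read as loss of microstructural integrity, and the only atrophy check protects PET.

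The direction follows from the stated method and from CSF having the higher diffusivity. The size cannot be settled: it rests on voxel size, CSF contact, alignment error and MD spread, none of which the documents give. Smaller volume alone contributes little. MD is one of several secondary markers, and the primary comparison of PET data between currently depressed patients and controls is not affected. The change is worth making because it costs almost nothing and the plan already produces the volume it needs.

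**What to change.** In Analysis of MRI data, state that MD is computed after excluding voxels with CSF-level MD, with the threshold fixed in advance, or as the median within the mask. Add an eroded mask as a check where enough voxels remain, and say whether the erosion is counted in diffusion or T1 voxels. If the cited procedures already contain such a step, say so instead.

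In Analysis of all data, keep the unadjusted MD result and report a sensitivity analysis beside it. This adjusts the MD group comparison for the volume of the same structure divided by total intracranial volume, and partials that volume out of the PET-MD correlation.

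The cost is a few lines of image-processing code and some wording, with no new scans. There are two small downsides: exclusion or erosion leaves fewer voxels, chiefly in the amygdala, and volume adjustment may remove some true effect where atrophy and microstructural change go together. For that reason the adjustment is a sensitivity analysis and both results are shown.

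### Two of the four named MRI outcomes, cortical thickness and default-mode connectivity strength, are replaced in the MRI analysis by measures that are not listed as outcomes

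*Protocol article*

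**What the plan says.** In the protocol article, the section Outcomes lists four MRI outcomes, each with its metric:

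- "structural (i.e., cortical thickness to quantify cortical atrophy");
- for diffusion, "the mean diffusivity for measuring microstructural integrity";
- for T2* relaxometry, R2* "for measuring intracerebral iron content";
- "resting-state functional MRI (i.e., default mode network connectivity strength").

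Secondary objective (iii), at the end of the Introduction, names the same four as the markers to be correlated with the TSPO distribution volume in the three groups.

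The section Analysis of MRI data then describes the processing. On structure: "Using T1 anatomical image, we will identify and segment hippocampi and amygdala". The volumes of these structures are divided by total intracranial volume, and mean diffusivity (MD) is averaged within the same masks. On function: "Individual correlation maps between the defined regions (hippocampus, amygdala, anterior cingulate gyrus, frontal cortex") and the whole brain, followed by a Fisher transformation and group t-tests. On movement in the diffusion data, after the MD maps have been registered to T1 by an affine alignment: "As a result of this processing, the MD maps were corrected for head movements".

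The section Analysis of all data adds a safeguard for reading the PET results: "Secondly, we will verify that there is no spatial collocation between the atrophy marker (MRI) and the inflammation marker". It then correlates the PET maps with the structural and functional MRI maps.

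**The concern.** An outcome list and its analysis section should describe the same quantities. Here, for two of the four MRI outcomes, the analysis section names a different measure in different anatomy. An analyst who follows it would report limbic volumes and limbic and frontal seed maps, and would have neither cortical thickness nor a default-mode value to report.

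Two things are at stake. First, secondary objective (iii) would be answered for measures other than those it names. A default-mode result, if wanted later, would have to be chosen after the fact from several seeds and whole-brain maps. Second, the atrophy check is meant to stop tissue loss from being misread as a PET effect. Most of the PET regions are cortical, and the marker that Outcomes assigns to atrophy is cortical thickness, whose derivation is not described.

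**Working it through.** No sample size, power or error rate is involved, so the check sets the sections side by side.

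| Marker in Outcomes and objective (iii) | What Analysis of MRI data derives | Match |
|---|---|---|
| Cortical thickness | Hippocampal and amygdalar volume / intracranial volume | No: a different measure, and not in the cortical regions at issue |
| Default-mode connectivity strength | Whole-brain maps from four seeds: hippocampus, amygdala, anterior cingulate, frontal cortex | No: no default-mode seed set, component or summary |
| R2* | Nothing described, and nothing put in its place | Silent |
| Mean diffusivity | Voxelwise MD maps; means in the hippocampus and amygdala masks | Yes, though regional means cover two structures only |

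Stated substitutions: 2 of 4. Silent: 1 of 4. Derived: 1 of 4.

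**Could the seed maps contain the default-mode outcome?** The anterior cingulate and frontal seeds may overlap that network, and a whole-brain map may show parts of it. But the stated purpose of the analysis is activity connected to the hippocampus, the amygdala and the prefrontal cortex. The network is not named in the section, and no single strength value per subject is defined to correlate with PET.

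**Atrophy check.** The section Analysis of PET imaging data lists 13 regions. Its word order is garbled. If it is read as precuneus, anterior and posterior cingulate, and frontal, temporal, parietal and occipital cortex, then 1 + 2 + 4 = 7 are cortical. For these seven the article describes no atrophy measure, because the only structural measures derived are the hippocampal and amygdalar volumes.

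**Head movement.** The order of steps given is: fit the tensor at each voxel, form the MD map, then align that map to T1 with one affine transformation. Movement between diffusion volumes affects the data before the fit. A single alignment of the finished map moves the whole map and cannot undo it. The sentence is therefore wrong as worded.

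**The case against.** The strongest reply is that this is a condensed article. It points to earlier procedures (references 67–70) and to a co-registration method already used by the team (reference 71), and none of these can be seen here. Analysis of all data also commits to testing each marker map and refers to an atrophy marker and to iron deposits, so the authors evidently expect those maps to exist.

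Much of this stands, and it rules out several stronger readings that a reader might infer:

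- *That three of the four outcomes are replaced.* For R2* nothing is substituted. Its processing is simply not described, which an article may leave to the full protocol.
- *That objective (iii) cannot be answered or the atrophy check cannot be done.* The T1 images are acquired and the cited procedures may include cortical thickness. The documents show only that its derivation is not described and that another measure is.
- *That only the hippocampus links MRI to PET, because it is the one segmented structure among the 13 PET regions.* The PET–MRI comparison is planned on co-registered maps, the MD maps are voxelwise, and the anterior cingulate and frontal cortex appear both as seeds and as PET regions.
- *That group differences in movement will remain in MD.* Motion correction may have been applied to the raw series under the cited procedures. The article does not say so, but it does not exclude it either.

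Condensation does not explain the thickness and default-mode points. There the article is not silent: it gives the processing in some detail and names other measures.

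**Conclusion.** The point holds for cortical thickness and default-mode connectivity strength: two of the four MRI markers in secondary objective (iii) are replaced by measures that are not listed as outcomes. As a consequence, the atrophy check has no described cortical atrophy measure. R2* is undescribed, which is a lesser matter. The head-movement sentence is wrong as worded, but no bias in MD is shown.

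The weight is moderate. A secondary objective is affected, and the primary PET comparison is touched only through the atrophy check that supports its interpretation. The conclusion assumes that the article's analysis section reflects what will be run. If the full protocol derives thickness and a default-mode summary, the article still needs correcting, because its sections do not agree.

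**What to change.** Bring Analysis of MRI data into line with Outcomes and objective (iii):

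1. Define one default-mode connectivity summary per subject, prespecified and computed in CONN, as the functional outcome. Label the hippocampal, amygdalar, cingulate and frontal seed maps exploratory.
2. Derive cortical thickness from the T1 images in the cortical PET regions. It does not exist for the putamen, the caudate or the semi-oval centrum, so use volume or MD in subcortical and white-matter regions.
3. Name these as the measures used in the atrophy check.
4. Add a line on how R2* is obtained, or refer to the document that says so.
5. Replace the head-movement sentence. State that motion and eddy-current correction is applied to the raw diffusion series before the tensor fit.

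If the volumes and seed maps are what the investigators really intend, the alternative is to relist those as the outcomes and amend objective (iii) and the atrophy check to match.

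The cost is modest: extra processing of scans already planned, with software already named for the functional part, and changes of wording. No further subjects or visits are needed.

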#### Analysis of all data

PET and MRI imaging, clinical symptomatology and biological markers. PET and MRI images will be co-recorded using a method previously used by our team (71) [e.g., 71] so that the maps of all multimodal markers have the spatial consistency needed for their statistical comparison. Firstly, for each marker map, we will perform *t*-tests to compare the groups with each other (SPSS 25.0). This will allow us to quantify the structural, functional and inflammatory alterations that characterize each group (i.e., treatment-resistant MDD vs. control, responsive MDD vs. control, treatment-resistant MDD vs. responsive MDD). Secondly, we will verify that there is no spatial collocation between the atrophy marker (MRI) and the inflammation marker (DPA714 -PET) that can induce a different interpretation of PET results. Finally, we will correlate the inflammation marker maps with the structural and functional marker maps generated with MRI. This will allow us to understand whether neuroinflammation is linked to brain changes (e.g., iron deposits, functional alteration).

To study the correlation between the severity of depressive symptoms, suicide risk and the intensity of neuroinflammation, graphic representations will be made to observe the distribution of these data in the two groups concerned. The Pearson correlation coefficient will be calculated in each instance. The same analysis strategy will be used to measure the correlation between plasma concentrations of biological markers of peripheral inflammation and the intensity of neuroinflammation in the three study groups.

